##### Virtual Reality (VR)

To investigate the influence of immersive environments on vaccine-related attitudes, it will employ a 3D virtual reality (VR) setup. Participants will experience a simulated vaccination scenario using the Oculus Rift system (Meta Platforms Inc., Menlo Park, CA, USA), which provides high immersion through high-resolution OLED displays, a 90 Hz refresh rate, and a 110° field of view. Motion tracking capabilities will facilitate realistic interaction within the environment, while integrated 3D spatial audio will enhance sensory engagement. A dedicated graphics workstation equipped with an NVIDIA Titan X graphics card will ensure seamless rendering and optimal performance.

##### Skin Conductance Response (SCR)

Skin conductance response (SCR) will be recorded to assess autonomic nervous system activation in response to vaccination-related and unrelated stimuli. Electrodermal activity (EDA) will be measured using Ag-AgCl electrodes affixed to the middle phalanges of the non-dominant hand, with isotonic gel applied to ensure a stable signal acquisition. Data will be collected using a Biopac MP36 system with a BioNomadix module transmitter, filtered with a 1 Hz low pass setting, and processed offline using Biopac’s Acknowledge 4.3 software.

### 2.7. Interventions

#### 2.7.1. Experiment 1

Prior to the experimental session, participants will complete demographic and psychological questionnaires. Following screening, the optimal scalp positions (OSP) and resting motor threshold (rMT) for the target (deltoid) and control (extensor carpi radialis) muscles will be determined. Participants will be seated 80 cm from a computer screen in a dimly lit room. The experimental visual stimuli will consist of pictures depicting scenes of vials and ongoing injections referring to blood sampling, COVID-19 vaccine, and influenza vaccine subtending a 10.5 × 5.8 cm region plus a neutral control stimulus consisting of a scrambled picture of the same dimension and form (see Figure 2).

For each type of stimulus in both blocks, 20 MEPs will be recorded. To ensure a balanced and unbiased presentation, stimuli will be randomly presented. A total of 16 MEPs per muscle and condition will be obtained and stored for offline analysis.

During stimulus presentation, TMS pulses will be delivered at 120% of rMT at randomized intervals (1100–1400 ms post-stimulus onset) to mitigate priming effects. EMG will record muscle activity from the levator labii superioris, which is associated with disgust responses, and the corrugator supercilii, linked to fear responses. Additionally, following the TMS session, participants will be presented again with the same set of pictures and will ask to rate their emotional responses using a 7-point Likert scale, where 1 indicated no emotional reaction and 7 indicated a very strong emotional reaction. Specifically, they were asked to evaluate the extent to which each image elicited feelings of alarm, disgust, fear, and anger.

#### 2.7.2. Experiment 2

Following the completion of demographic and psychological questionnaires, participants will be immersed in a virtual reality (VR) environment for a Pavlovian fear conditioning and extinction task created by our group [45,46]. The paradigm consists of three phases—habituation, acquisition, and extinction, conducted over one day. During habituation, participants will observe two colored doors (blue and red) presented in a randomized order across eight trials. In the acquisition phase, the blue door (CS+) will be paired with an aversive stimulus—an approaching, screaming monster (80 dB)—in 80% of trials, while the red door (CS−) will not be associated with any aversive event. Ten minutes after acquisition, the extinction phase will begin. During this phase, the blue door (CS+) will no longer be followed by the aversive stimulus, allowing participants to experience its diminished threat value. Extinction will last approximately ten minutes and contain 20 trials. The recall session will occur 24 h later, during which the same blue door (CS+) will again be presented without any aversive stimulus. Throughout the experiment, participants will rate the perceived fearfulness of each stimulus using a 10-point Likert scale (1 = not scary at all; 10 = extremely scary). Typical CS− and CS+ sequences during the acquisition phase can be found in Lucifora et al. [47]. Participants scoring high on the State-Trait Anxiety Inventory will be excluded from the experiment.

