##### Transcranial Magnetic Stimulation (TMS) and Motor Evoked Potentials (MEPs)

To determine the optimal scalp positions (OSP) for stimulation, transcranial magnetic stimulation (TMS) will be applied using a 70 mm figure-of-eight coil connected to a MagStim Super-Rapid stimulator (The Magstim Company, Wales, UK) placed over the left M1. MEPs will be recorded via a Biopac MP-36 (BIOPAC Systems, Inc., Goleta, CA, USA) electromyographic system. Ag-AgCl Self-adhesive surface electrodes (15 × 20 mm diameter) will be placed over the right deltoid (target muscle, reference over the acromion process) and the right extensor carpi radialis (ECR; control muscle, reference over the dorsal wrist). We will place the ground electrode over the right elbow. The ECR was selected as the control muscle because, like the deltoid, it is located in the upper limb, allowing for topographically matched comparisons within the same somatomotor cortical region. In the context of MEPs elicited via TMS, this is critical: upper limb muscles are represented adjacently in the lateral primary motor cortex, allowing for consistent stimulation parameters (e.g., coil orientation, hotspot location) and minimizing anatomical confounds.

The coil will be held tangentially to the scalp, with the handle oriented at approximately 45° posterolaterally to the midline, in accordance with standard procedures for optimal activation of the primary motor cortex [38,39].

The coil will be systematically shifted in 1 cm increments over the motor cortex to identify the OSP for each muscle, which will be marked on the scalp using a makeup pencil. Once the OSP is determined, the resting motor threshold (rMT) will be established, defined as the lowest stimulation intensity capable of eliciting at least five MEPs of ≥50 μV in amplitude across ten consecutive magnetic pulses. EMG signal will be continuously recorded throughout the experimental session to confirm the absence of muscular pre-activation. It will be band filtered (5 Hz–2.5 kHz, sampling rate 10 kHz), digitalized, and stored for offline analysis. To ensure comparability across participants, all MEP amplitudes will be log-transformed (log value in mV + 1) to reduce skewness. Mean MEP amplitudes for each condition will be then normalized and expressed as a % of the baseline.

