##### Electromyography (EMG)

EMG signals will be recorded using a BIOPAC MP-36 system (BIOPAC Systems, Inc., Goleta, CA, USA). The signals will be amplified (×1000) and filtered with a 100–500 Hz bandpass. Electrodes will be positioned on the left side of the face, targeting the levator labii superioris (associated with disgust) and the corrugator supercilii (associated with fear), following standard placement guidelines [44]. We will remove artifacts commonly associated with facial EMG recordings. Specifically, the EMG signals will be visually inspected for non-physiological spikes, eye blinks, speech-related artifacts, or excessive movement. Trials containing artifacts (e.g., signals exceeding ±3 SD from baseline) will be excluded from further analysis. If >25% of trials from a given condition are affected, the participant will be excluded from that analysis. Finally, a baseline correction will be applied relative to a pre-stimulus window to account for tonic muscle activity.

#### 2.6.2. Experiment 2

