### 2.8. Statistical Methods

All statistical analyses will be conducted using Jamovi (version 2.6.23), an open-source statistical software based on the R 4.5.0 framework. A significant threshold of *p* < 0.05 will be applied to all analyses. Parametric methods will be employed under the assumptions of normality and homogeneity of variance, verified by Shapiro-Wilk or Kolmogorov-Smirnov and Levene’s tests, respectively. Non-parametric tests will be used if assumptions are violated.

#### 2.8.1. Experiment 1

A 2 × 2 × 3 mixed-design ANOVA will be conducted to analyze differences in MEP amplitudes, with group (Vax vs. No-Vax) as a between-subjects factor, muscle (deltoid vs. extensor carpi radialis), condition (Blood, COVID-19, influenza), as within-subjects factors.

EMG activity from the levator labii superioris (disgust) and corrugator supercilii (fear) will be analyzed using a 2 × 2 × 3 mixed-design ANOVA, incorporating group (Vax vs. No-Vax), muscles (levator labii superioris, corrugator supercilii), condition (Blood, COVID-19, influenza).

Significant interactions (*p* < 0.05) will be followed by Tukey’s HSD post hoc tests to identify condition-specific effects.

#### 2.8.2. Experiment 2

Habituation, fear acquisition, extinction, and recall will be assessed through Skin Conductance Response (SCR) amplitudes using a 2 × 2 × 3 mixed-design ANOVA. The analysis will compare responses to stimuli (CS+ threat-associated stimulus, CS− safety-associated stimulus) as a within-subjects factor, across groups (Vax vs. No-Vax) as a between-subjects factor and phases (habituation, fear acquisition, fear extinction) as a within-subjects factor. Similarly, subjective fear/disgust ratings (Likert scale) will be analyzed using a 2 × 2 × 3 mixed-design ANOVA, with group (Vax vs. No-Vax) as a between-subjects factor, and stimulus Type (CS+ vs. CS−) and phase (habituation, fear acquisition, fear extinction) as within-subjects factors. Significant interactions (*p* < 0.05) will be followed by Tukey’s HSD post hoc tests to identify condition-specific effects.

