## 3. Discussion

This study aims to provide novel insights into the psychophysiological correlates of vaccine hesitancy (VH). Grounded in the Somatic Marker Hypothesis [25], we hypothesize that bodily and emotional responses will play a crucial role in shaping vaccination attitudes. By investigating sensorimotor mapping, affective learning processes, and psychological predictors of VH, we seek to contribute to a more comprehensive understanding of this phenomenon.

### 3.1. Experiment 1

We predict significant differences in motor evoked potentials (MEPs) between vaccine-hesitant and vaccine-accepting individuals when exposed to COVID-19 vaccination imagery. Specifically, hesitant individuals may exhibit reduced MEP amplitudes in the deltoid muscle—a key muscle involved in vaccine administration—suggesting altered sensorimotor resonance in response to vaccination stimuli. This would align with previous research on embodiment, which posits that motor responses are modulated by observed actions [48,49]. The sensorimotor resonance may serve as a proxy for embodied affective states such as disgust or fear—emotions that are central to the Somatic Marker Hypothesis, which emphasizes the role of visceral and emotional signals in guiding behavior and cognition [25]. Therefore, a decrease in MEP amplitude may indicate a disruption of somatic marker signals, given that corticospinal excitability is sensitive to modulation by negative emotional states. This interpretation is supported by prior work demonstrating the influence of emotions—particularly aversive or defensive states on motor system activity [39,40,41,50,51,52,53]. We suggest that motor resonance changes, in this context, may index the embodied affective experience central to the SMH, thereby linking motor excitability to emotional and interoceptive processing.

Additionally, we anticipate increased facial electromyography (EMG) activity in the levator labii superioris and corrugator supercilii muscles in vaccine-hesitant individuals, reflecting higher levels of disgust and fear responses. If confirmed, these results would support the hypothesis that VH is influenced by affective biases linked to disgust sensitivity and anxiety [9,21].

### 3.2. Experiment 2

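### The scrambled picture has no role in the facial EMG analysis, so a group main effect there cannot be separated from general reactivity to any picture

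*Protocol article*

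**What the plan says.** Section 2.7.1 describes the Experiment 1 stimuli as vial and injection scenes for blood, COVID-19 vaccine and influenza vaccine, "plus a neutral control stimulus consisting of a scrambled picture of the same dimension and form". It adds: "For each type of stimulus in both blocks, 20 MEPs will be recorded". The scrambled picture belongs to the stimulus set, and facial EMG is recorded during stimulus presentation. By implication, facial EMG exists for the scrambled trials too.

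Section 2.8.1 analyses facial EMG in a 2 × 2 × 3 mixed ANOVA with group, "muscles (levator labii superioris, corrugator supercilii), condition (Blood, COVID-19, influenza". A significant interaction "will be followed by Tukey’s HSD post hoc tests to identify condition-specific effects". No stated facial EMG analysis uses the scrambled picture.

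The only reference for facial EMG is in section 2.6.1, under Electromyography: "a baseline correction will be applied relative to a pre-stimulus window to account for tonic muscle activity".

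The prediction in section 3.1 is "we anticipate increased facial electromyography (EMG) activity in the levator labii superioris and corrugator supercilii muscles in vaccine-hesitant individuals". It names both muscles and no condition. The same section says that confirmation would support an affective account based on disgust sensitivity and anxiety.

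**The concern.** The sentence in 3.1, read as written, is a group main effect: a higher level in the hesitant group, in both muscles, over whatever pictures are analysed. Two different states of affairs produce it. In one, hesitant people react more to medical pictures. In the other, their faces react more to any picture appearing on a screen.

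The pre-stimulus correction removes resting tone and any sustained tension from the TMS setting. It does not remove a phasic response to picture onset. The scrambled picture is the one stimulus in the design that could measure that response, and the analysis does not use it. A significant group effect could then be read as disgust or fear when it is non-specific.

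**Working it through.** **No figure in the plan to reproduce.** The protocol gives no number on this point. The passages establish the gap, and the arithmetic below only illustrates its consequence.

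**Inputs.** From the protocol: 20 per group, two-sided α = 0.05, three medical conditions, one scrambled picture. Assumed: a group shift of 0.5 or 0.8 SD and the variance structure. Two structures are used, for scores averaged over the two facial muscles:
- A: between-person variance 0.5, within-person variance 0.5 (total SD 1, correlation 0.5). Section 2.1.2 assumes 0.5 for the MEP measurements; it is borrowed here.
- B: between-person variance 1, condition noise SD 0.5, so within-person variance 0.25 (correlation 1/1.25 = 0.8). Shifts are in units of the between-person SD.

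**Formulas.** With between-person variance b and within-person variance w:
- Mean of the three medical conditions: variance b + w/3.
- That mean minus scrambled: variance w(1 + 1/3) = 4w/3.
- Two-group t test, 38 df: noncentrality = (shift/SD) × √(20/2).

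**Case 1: general reactivity only.** The shift applies to every picture, including the scrambled one.

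| Structure | Shift | SD of 3-condition mean | Noncentrality | Group main effect significant | Medical minus scrambled |
|---|---|---|---|---|---|
| A | 0.5 | √0.667 = 0.816 | 1.94 | 47% | 5% |
| A | 0.8 | 0.816 | 3.10 | 86% | 5% |
| B | 0.5 | √1.083 = 1.041 | 1.52 | 32% | 5% |
| B | 0.8 | 1.041 | 2.43 | 66% | 5% |

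The last column is the nominal level, because the shift cancels in the subtraction. Simulation agrees to within about a percentage point.

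**Case 2: what the interaction can and cannot do.** Structure A, 0.8 SD, 20,000 simulated trials:

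| True pattern in the hesitant group | Group main effect, 3 levels | Group × condition, 3 levels | Group × condition, 4 levels |
|---|---|---|---|
| Higher to every picture | 85% | 5% | 5% |
| Higher to all three medical pictures, not scrambled | 86% | 5% | 73% |
| Higher to both vaccine pictures, not Blood | 52% | 73% | 85% |
| Higher to COVID-19 only | 18% | 73% | 73% |

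In the planned three-level analysis the first two rows give the same result. They separate only once the scrambled picture is a level. The last two rows are already distinguishable from the first without it.

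**Power of the contrast.** For a true 0.8 SD excess to the medical pictures only, medical minus scrambled detects 86% under A (SD √0.667 = 0.816) and 99% under B (SD √0.333 = 0.577). It is less noisy than the group main effect when 4w/3 < b + w/3, that is when w < b, or correlation above 0.5. Below 0.5 it is noisier.

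**The case against.** The strongest reply is that Blood is already a non-vaccine comparator. The planned group by condition interaction with Tukey follow-up separates a vaccine-specific excess from general reactivity, as the last two rows of the second table show. This stands. A reader might infer that, without the scrambled picture, no facial EMG finding can be told apart from general reactivity. The protocol does not support that. The ambiguity is confined to the group main effect and to an excess shared by all three medical pictures. Blood does not close that remaining gap, because it is itself an injection or vial scene. The protocol's own mechanisms in sections 1 and 2.5 (needle phobia, disgust at bodily invasion) would raise the response to Blood as well.

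Second, the abstract attaches the stronger affective response to vaccination pictures, and 2.8.1 does not name the group main effect as the confirmatory facial EMG test. This is fair. The point rests on the wording in 3.1 and on how a main effect would be interpreted.

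Third, a reader might infer that the control picture goes unused for MEPs too. That cannot be concluded. The MEP ANOVA has the same three levels, "muscle (deltoid vs. extensor carpi radialis), condition (Blood, COVID-19, influenza), as within-subjects factors", but section 2.6.1 says "Mean MEP amplitudes for each condition will be then normalized and expressed as a % of the baseline" without defining the baseline. The scrambled trials may already be the denominator. For MEPs this is a point of clarity only.

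Fourth, a scrambled image has no recognisable content. Medical minus scrambled removes reactivity to picture onset, but not reactivity to any meaningful or medical image. This also stands, and it is why the contrast cannot replace vaccine versus Blood.

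Fifth, the rejection rates follow from shifts that were put in by assumption. They show that the planned main effect cannot discriminate; they do not show that hesitant people have more reactive faces.

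**Conclusion.** The concern holds in a limited form. As section 2.8.1 stands, a group main effect on facial EMG, or an excess common to blood, COVID-19 and influenza pictures, cannot be attributed to medical content rather than to phasic reactivity to any picture. A vaccine-specific excess over Blood remains testable as planned.

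For a purely general difference of 0.8 SD, the main effect would be significant in about 66% to 86% of trials (32% to 47% at 0.5 SD), against about 5% for the contrast with the scrambled picture. The shifts and variance structures are assumptions; the protocol gives no facial EMG variance. The omission itself needs no assumption, because it is visible in the stated factor levels.

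**What to change.** In section 2.8.1, either add Neutral (scrambled) as a fourth level of the facial EMG condition factor and test group × (medical pictures versus neutral), or analyse each condition minus the same participant's scrambled-picture response for that muscle. Keep vaccine versus Blood, by group, as the test of vaccine specificity, and say that medical minus scrambled alone does not show a vaccine-specific response. In section 3.1, state which of these contrasts the facial EMG prediction refers to.

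The cost is a sentence or two, and the design already plans to collect the data. The subtraction adds some within-person noise: the within-person part of the variance goes from w/3 to 4w/3. In return the between-person part drops out, so there is a net loss of precision only if the correlation between conditions is below 0.5.

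As a secondary clarification, section 2.6.1 should say what the MEP baseline is, and whether it is the scrambled trials.

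### In Experiment 2 the CS+ is the blue door and the CS− the red door with no counterbalancing stated, so door colour is aliased with CS role in the stimulus main effect and in single-phase CS+/CS− comparisons

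*Protocol article*

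**What the plan says.** Section 2.7.2 of the protocol article ties colour to role at every stage of the task.

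- Habituation: "participants will observe two colored doors (blue and red) presented in a randomized order across eight trials".
- Acquisition: "the blue door (CS+) will be paired with an aversive stimulus", whereas "the red door (CS−) will not be associated with any aversive event".
- Extinction: "the blue door (CS+) will no longer be followed by the aversive stimulus".
- Recall, 24 hours later: "the same blue door (CS+) will again be presented without any aversive stimulus". The red door is not mentioned here.

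The only randomization described in the task is the order of the doors in habituation. Nothing says that the colour given the CS+ role varies between participants.

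Section 2.8.2 then specifies, for SCR: "The analysis will compare responses to stimuli (CS+ threat-associated stimulus, CS− safety-associated stimulus) as a within-subjects factor". Group is the between-subjects factor, and phase (habituation, acquisition, extinction) is the second within-subjects factor. The ratings are analysed in the same way, and significant interactions are followed by Tukey tests.

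**The concern.** With a single mapping, CS role and door colour are the same column of the design matrix. A larger response to the CS+ than to the CS− can come from learning, from a difference in how people respond to blue and red, or from both. If red is the more arousing colour, the safety comparator is raised and conditioning is understated in both groups. If blue is learned as a threat cue more readily, conditioning is overstated.

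The group comparison is exposed by a narrower route. The groups are formed by attitude and not by allocation, and Section 3.2 expects them to differ on disgust sensitivity, paranoia and dogmatism. If they also respond differently to the two colours, that difference could be read as a difference in fear learning.

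The aliasing is built in when the data are collected. No later analysis can undo a colour effect that arises after habituation.

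**Working it through.** **Inputs.** 20 participants per group (Section 2.2.1); two stimuli, three phases and two groups (Section 2.8.2); correlation 0.5 among the six measurements (Section 2.2.2). The documents give no colour or conditioning effect in SD units, so 0.5 SD is assumed throughout for illustration. No figure in the plan needs reproducing on this point.

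**Step 1: what each term estimates.** Let k_p be the true conditioning effect (CS+ minus CS−) in phase p, with k_H = 0 in habituation, and c_p the colour effect (blue minus red). With blue always CS+, the observed difference is D_p = k_p + c_p.

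- Single-phase comparison: k_p + c_p, so colour enters one for one.
- Stimulus main effect: mean(k_p) + mean(c_p), likewise.
- Stimulus × (acquisition − habituation): k_A + (c_A − c_H). A constant colour effect cancels; a changing one does not.
- Group × stimulus: the group difference in mean(k_p) plus the group difference in mean(c_p).
- Group × stimulus × (acquisition − habituation): the group difference in k_A plus the group difference in (c_A − c_H).

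**Step 2: colour effect the same in both groups.** Simulation with SD 1 and 4000 runs; rejection rate at 0.05, with the mean estimate in brackets where available.

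| Scenario (0.5 SD) | Stimulus main effect | Stimulus × (acq − hab) | Group × stimulus × (acq − hab) |
|---|---|---|---|
| Constant colour effect, no conditioning | 100% (0.50) | 5.2% (0.00) | 5.3% |
| Colour effect in acquisition only, no conditioning | 43.1% (0.17) | 58.1% (0.50) | 5.4% |
| True conditioning in acquisition, no colour effect | 42.0% (0.17) | 58.0% (0.50) | 4.7% |

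In the first row, the habituation difference recovers the colour effect (0.50). The second and third rows cannot be told apart.

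The rates agree with direct arithmetic. With SD 1 and r = 0.5, each D_p has variance 0.5 + 0.5 = 1.

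- Main effect: SE = √((1/3)/40) = 0.091, and 0.5/0.091 = 5.5.
- Change from habituation: SE = √(2/40) = 0.224, and 0.5/0.224 = 2.2.

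**Step 3: colour effect in one group only, no conditioning.**

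- Constant over phases: group × stimulus is rejected in 75.7% of runs (estimate 0.50). Arithmetic: SE = √((1/3) × 2/20) = 0.183, and 0.5/0.183 = 2.7. The effect cancels in the three-way term.
- In acquisition only: the three-way contrast is biased by 0.50. SE = √(2 × 2/20) = 0.447 and 0.5/0.447 = 1.1, which gives about 19% rejection on 38 degrees of freedom.

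**Step 4: the same constant one-group effect with 10/10 counterbalancing.** D_p = k_p + c_p for blue-CS+ participants and k_p − c_p for red-CS+ participants, so the average is k_p. The group × stimulus estimate is 0.00 and rejection is 2.0%. That rate is below 5% because unmodelled colour inflates the within-group spread. With assignment and its interaction with group in the model, rejection returns to about 5%.

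**The case against.** The strongest reply is that the study question is a comparison of groups that receive the same mapping. A colour effect common to both drops out of group × stimulus and of the three-way term, even when it acts on learning: the group contrast stayed at 5.3% to 5.4% in both common-colour scenarios. Habituation also gives an unreinforced baseline for both doors and is a level of the phase factor. Nothing in the documents links the groups' expected traits to responses to blue or red. A fixed mapping gives everyone the same task and avoids some between-person variance. All of this stands, and it limits the point.

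It does not remove the point. Section 2.8.2 does not confine inference to change from habituation: the stimulus main effect is part of the planned ANOVA, and a Tukey comparison of CS+ with CS− inside acquisition or extinction subtracts no baseline. Equal colour response in two self-selected groups is an untested assumption.

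One might also say that the article is condensed and refers to the group's earlier work for the task. But the mapping is stated positively in acquisition, extinction and recall, so this is not a silence that the full protocol would fill. That it holds for every participant is the natural reading, though not an express statement.

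Counterbalancing has a limit too. If one colour conditions more readily, it averages two conditioning strengths and does not abolish the difference.

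**Conclusion.** The aliasing of colour with CS role is complete in the stimulus main effect and in single-phase CS+/CS− comparisons. In stimulus × phase it remains only for colour effects that emerge or change after habituation. The group contrasts are at risk only under a group × colour effect, and the three-way term only if that effect also changes with phase.

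A reader might infer that no colour effect can be separated from conditioning, or that every Experiment 2 result is compromised. The documents support neither. A constant colour effect can be estimated from habituation and cancels in stimulus × phase, and a colour effect shared by the groups does not create a group difference. Not every prediction rests on the CS−, either: Section 3.2 predicts a higher response to the CS+ itself.

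The simulated rates rest on the assumed 0.5 SD, SD 1 and r = 0.5, and show the mechanism, not a likely size. The point is a cheap and worthwhile improvement, not a flaw that invalidates the group comparison.

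**What to change.** Before data collection, counterbalance the CS+ colour within each group: 10 participants with blue as CS+ and 10 with red, from a pre-generated list stratified by group. Keep each participant's assignment through extinction and recall. Code the stimulus factor by CS role, and enter colour assignment as a between-subjects term with its interactions with group and stimulus. State that inference on conditioning rests on the stimulus × phase change from habituation, not on the stimulus main effect or single-phase contrasts.

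The cost is a colour swap in the virtual reality task and one assignment list, with no added participants or sessions. The downsides are slightly more between-person variance if colour matters (largely recovered by the colour term) and less exact comparability with the group's earlier fixed-colour task. Colour cancels exactly only if the 10/10 balance survives exclusions into the analysed data; otherwise the colour term has to carry the adjustment.

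If the mapping has to stay fixed, report the habituation blue-minus-red difference by group, use the change from habituation, and state that a colour effect on learning cannot be excluded.
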